**Figure 4 F4:**
[figure not shown]
Fracture Risk Assessment (FRAX), sample size and power calculations for Picking up Hidden Osteoporosis Effectively during Normal CT Imaging without additional X-rays (PHOENIX). (A) FRAX UK age-specific fracture risk assessment and intervention thresholds. (B) Age-specific prevalence of red/amber FRAX risk category from preliminary local application of PHOENIX intervention in Cambridge. (C) Calculation of the number of invites needed to randomise 375 red/amber risk participants based on different responses (rates of agreeing to participate). (D) Number of PHOENIX invitation packs that must be given out in order to randomise 375 red/amber risk participants based on different prevalence of red/amber FRAX among participants. (E) Our feasibility study aiming to randomise 375 of 938 (40%) consenting participants (ie, 30% of 3125 total invited) would estimate the trial’s response rate with a precision of 1.6% (ie, half-width of the 95% CI, *this sample size having 80% power to reject null hypothesis at a 30% response*). (F) The randomised sample of 375 patients will provide 80% power to detect a difference of at least 6% or larger in the 12-month overall trial retention rates from a hypothesised 75% retention, based on two-sided one-sample test of proportion at 5% significance level (ie, providing statistical evidence that the overall retention may be as low or high as 69% (0.69) or 81% (0.81) respectively, as opposed to 75%, 0.75=*sample size for 80% power to reject null hypothesis of 75% retention*). (G) Power versus sample size to detect differences in 12-month treatment rates in our three-arm trial, assuming treatment percentages of 4.5% vs 15.5% vs 20.3% with 1:1:1 randomisation to usual care versus active control FRAX-GP versus PHOENIX intervention, respectively, and type 1 error=0.05.

#### Power for recruitment and retention

Hypothesising that the recruitment (ie, consent, FRAX completion, eligibility and CT imaging, ie, ‘response’) would be similar to that observed in the SCOOP primary prevention trial (p0=30%); a feasibility study aiming to randomise 375 of 938 (40%) consenting participants (ie, 30% of 3125 total invited) would estimate the trial’s response rate with a precision of 1.6% (ie, half-width of the 95% CI, figure 4E). The randomised sample of 375 patients will provide 80% power to detect a difference of at least 6% or larger in the 12-month overall trial retention rates from a hypothesised 75% retention (as with the SCOOP trial) based on two-sided one-sample test of proportion at 5% significance level (ie, providing statistical evidence that the overall retention may be as low or high as 69% (0.69) or 81% (0.81), respectively, as opposed to 75%, 0.75, figure 4F). In addition, against the same expectation, the 1:1:1 randomised comparison (ie, PHOENIX intervention vs active control FRAX to GP vs usual care pathways) will have >80% power to detect at least 12.2% absolute difference in retention rates between trial arms (or RR=1.16) based on two-sided two-sample test of proportion at 5% significance level.

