## Methods and analysis

This feasibility study aims to test our PHOENIX intervention, which begins by offering adults attending hospitals for CT (for any reason) a comprehensive bone health screen, followed by ‘opportunistic’ reuse of their CT scans for bone densitometry. The intervention ends with their GPs receiving detailed written advice on managing the participants’ bone health. Patients are offered an invitation pack comprising a novel informed consent form/data capture tool that the patient can fill out with or without assistance, and a participant information sheet. Specifically, we want to determine whether it is feasible for our team to undertake a large trial of the PHOENIX intervention to prevent fractures in a larger population of CT attenders. Hence, our co-primary outcome measure is our ability to randomise 375 ‘high-risk’ participants within 10 months. For the larger fracture prevention trial to be feasible, the other co-primary outcome measure must be achieved, which is retention at 12 months; our ability to record bone active treatment data (yes/no) in 75% of surviving patients. Power calculations for any future trial will be informed by the secondary outcome measure; the percentage of participants in each arm who have (i) received a treatment recommendation (due to osteoporosis, vertebral fracture or high FRAX risk) and (ii) received and commenced treatment 12 months after their CT scan. Box 2 contains a summary of the key features of the study protocol.

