Box 2Summary of key features of the Picking up Hidden Osteoporosis Effectively during Normal CT Imaging without additional X-rays (PHOENIX) study protocolPragmatic featuresPatients attending CT waiting rooms are offered a PHOENIX invitation pack comprising a novel informed consent form/data capture tool to ascertain Fracture Risk Assessment (FRAX) score (online supplemental file 1) that the patient can fill out with or without assistanceThe intervention (tested in group 1) comprises (i) retrieving the CT scans of those ‘amber’ or ‘red’ risk individuals with moderate to high 10-year fracture risk by FRAX, (ii) hip and spine bone mineral density analysis with vertebral fracture assessment and (iii) sending the general practitioner (GP) guidance from a clinical decision tree.The intervention take place ‘behind the scenes’ without impacting on patient flow or the radiography/radiology workflow.Data (imaging, clinical risk factor, Patient Identifiable Information (PID) including sensitive clinical information) flow via secure encrypted and approved methods including the NHS Image Exchange Portal, Picture Archiving and Communications System (PACS) and nhs.net secure clinical email.Technical staff can ‘pull’ clinical CT images for assessment at any time.Primary outcome measures/end pointsFeasibility of recruitment: defined as ability to randomise 375 ‘at-risk’ participants over continuous 10-month period.Retention: defined as retaining 75% of surviving participants to 12 months postrandomisation, proven by receipt of follow-up postal questionnaire (specifically an answer to the bone active medication received; yes/no question).Secondary outcome measures/end pointsNew vertebral fracture identification across three arms assessed at 12 months.Osteoporosis identification across three arms assessed at 12 months.Bone active medication initiation across the three arms assessed at 12 months.Survival at 12 months across three arms assessed at 12 months.Inclusion criteria: participants eligible for the trial should fulfil all of the following at randomisation:Attending for a routine clinical CT scan.Able to provide informed consent.Aged ≥65–90 years (women) or ≥75–90 years (men) attending for CT for any clinical reason, where the spine and/or hips are visible in scan images.Exclusion criteriaMetalwork in hips (due to streak artefact on the contralateral hip within CT).Known to be receiving prescription treatment for osteoporosis other than calcium/vitamin D (ie, bisphosphonate drug, strontium ranelate, denosumab, raloxifene or teriparatide since it would be futile to identify already known and treated osteoporosis).Prone CT scan (which cannot currently be processed by the software).Role of patients and the publicActively participated in the study design in focus groups within the project team.Assisted in the design of data collection tools, including the informed consent form and information leaflet.Provided guidance on the acceptability of approaching participants in CT scan areas and insight into the anxiety of attending hospital among some more elderly members of society. Adding country of origin and ethnicity questions to consent form to facilitate FRAX.Impact of COVID-19 pandemicRecruitment had to be paused due to the COVID-19 pandemic, then restarted in just one centre without face-to-face contact with patients. Therefore, recruitment was either by clinical approach/discussion versus self-consent based on just handing out recruitment packs after COVID-19 restrictions were brought in.

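### The 80% power stated for the retention test is about 75% at 69% and 79% at 81% with 375 patients, and lower on the survivor denominator that the co-primary uses

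*Protocol article*

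**What the plan says.** Under Power for recruitment and retention, the article states: "The randomised sample of 375 patients will provide 80% power to detect a difference of at least 6% or larger" in overall 12-month retention. The reference value is 75%, taken from the cited community screening trial (SCOOP), and the calculation is "based on two-sided one-sample test of proportion at 5% significance level". The result is described as statistical evidence that "the overall retention may be as low or high as 69% (0.69) or 81% (0.81), respectively", as opposed to 75%. The caption of figure 4F repeats the claim.

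The outcome itself is defined differently. Box 2 gives retention as "defined as retaining 75% of surviving participants to 12 months postrandomisation, proven by receipt of follow-up postal questionnaire". The Abstract and the opening of Methods and analysis also use survivors as the denominator. Methods and analysis makes the outcome decisive: "For the larger fracture prevention trial to be feasible, the other co-primary outcome measure must be achieved".

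**The concern.** Three things do not fit together.

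- **Power.** The stated 80% is not what the stated test delivers at 69%, which is the side that matters for feasibility.
- **Denominator.** The power uses everyone randomised, whereas the outcome uses survivors. The Strengths and limitations list says the primary outcome was amended because pandemic recruitment was expected to skew towards the more seriously ill, so deaths are not negligible here.
- **Rule.** The outcome is a pass mark on observed retention, but the only one-sample inference offered for retention is a two-sided test against that same 75%. Such a test can reject 75%. It does not show that retention is 69% or 81%.

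Progression to the fracture trial depends on this outcome, so readers need to know how informative the result will be and on which denominator.

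**Working it through.** **Inputs.** p0 = 0.75, p1 = 0.69 or 0.81, n = 375, two-sided 5% one-sample test of a proportion, stated power 80% (Power for recruitment and retention; figure 4F caption). The pass mark is 75% of survivors (Box 2). The article gives no death rate, so 5% and 10% are assumptions used to show a range.

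**1. Rejection limits at n = 375.** 0.75 ± 1.96 × √(0.75 × 0.25/375) = 0.75 ± 1.96 × 0.02236 = 0.75 ± 0.0438. The test rejects below 70.6% or above 79.4%. In counts, the exact equal-tail test rejects at 264 or fewer, or 298 or more.

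**2. The plan's own figure.** Power = Φ[(|p1 − p0| − 1.96 √(p0(1 − p0)/n)) / √(p1(1 − p1)/n)].

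- At 69%: (0.06 − 0.0438)/√(0.69 × 0.31/375) = 0.01617/0.02388 = 0.677, so power is 75.1%. Exact binomial: 73.8%.
- At 81%: 0.01617/√(0.81 × 0.19/375) = 0.01617/0.02026 = 0.798, so power is 78.8%. Exact binomial: 79.6%.

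The stated 80% is reproduced closely at 81% but not at 69%. Other two-sided versions at 69% (Wald, null variance only, arcsine, and exact rejection probabilities of the score and Wald tests) give 70.0% to 76.5%; adding a continuity correction lowers the figures further. Only a one-sided Wald version comes near 80% (80.7%), and the text says two-sided. Solving the formula for 80% power at n = 375 gives alternatives of 68.6% and 81.1%. For 80% power at exactly 69% or 81%, n would have to be 426 or 387.

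**3. Survivor denominator, same formula.**

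| Deaths (assumed) | n | Power at 69% | Power at 81% |
|---|---|---|---|
| 0% | 375 | 75.1% | 78.8% |
| 5% | 356 | 73.0% | 76.5% |
| 10% | 338 | 70.9% | 74.2% |

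**4. Test against pass mark.** 75% of 375 is 281.25, so the mark is met at 282 or more. From 265 to 281 retained (70.7% to 74.9%), the target is missed but the test does not reject 75%.

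**5. Chance of meeting the mark (binomial).**

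- If true retention among survivors is 75%: 0.492 with n = 375 (282 or more), 0.528 with n = 356 (267 or more), 0.504 with n = 338 (254 or more).
- If 75% is expected of all randomised and deaths fall within the 25% loss: with 5% deaths, survivor retention is 0.75/0.95 = 78.9% and the chance is 0.969 (n = 356). With 10% deaths it is 0.75/0.90 = 83.3% and the chance is close to 1.

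**The case against.** The strongest reply is that the shortfall is rounding: 68.6% and 81.1% print as 69% and 81%, and the detectable differences of 6.4 and 6.1 points print as 6%. That is fair for n = 375 and makes this part minor. It does not cover the further loss on the survivor denominator.

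A second reply is that the test and the pass mark answer different questions, and that a simple minimum target is a usual feasibility design. This also stands: the article does not attach the test to the decision, so there is no formal contradiction. What remains is that the only one-sample power statement for retention says nothing about the chance of meeting the target.

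Three stronger readings are tempting, but the article does not support them:

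- **That the study was sized on the retention test.** Sample size calculations, study power, randomisation method says that 12-month treatment rates helped set the target. The retention text reports what 375 provides, although the figure 4F caption calls it a sample size for 80% power.
- **That a trial running to plan fails half the time.** This needs 75% to be the expectation among survivors. If it refers to all randomised, the target is passed about 97% of the time with 5% deaths. The article does not say which is meant. Any cut-off is also met about half the time when the truth equals it; at a true 77% the rule passes 81% of the time with n = 375.
- **That a joint pass probability for both co-primaries can be had by treating recruitment as a draw from 3125 invitations.** That number is one scenario. The recruitment outcome is 375 randomised in 10 months, and nothing caps invitations.

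**Conclusion.** The power statement needs correcting, and the correction is modest. With 375 patients, power is about 75% at 69% and 79% at 81%, against the stated 80%. With 5% to 10% deaths (assumed) it is about 73% to 71% at 69% and about 77% to 74% at 81%. The power text and the co-primary use different denominators, and the sentence on evidence for 69% or 81% claims more than rejecting 75% can show.

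The chance of meeting the 75% target under the plan runs from about one half to near certainty, depending on a denominator the article does not state. That is a reason to state it, not proof that the target is badly set.

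**What to change.** - Restate the power as about 75% (at 69%) and 79% (at 81%) for n = 375, and add the lower values for survivors over a stated range of deaths. Amend the figure 4F caption to match.
- Say whether the 75% expectation refers to survivors or to all randomised.
- Replace the wording on evidence for 69% or 81% with a statement that the test can reject 75%.
- Report observed survivor retention with its 95% CI beside the 75% target.

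The pass mark can stay. Replacing it by a rule that stops only when the upper 95% limit is below 75% is a trade-off, not a correction: at a true 70%, such a rule (264 or fewer of 375) stops 59% of the time, whereas the present mark is passed only 1.5% of the time.

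The cost is wording, with no extra patients. The downside is that the published power looks slightly less favourable.

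### The stated power of over 80% for a 12.2-point retention difference between arms is about 70% for any two arms of 125

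*Protocol article*

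**What the plan says.** The section on power for recruitment and retention makes two statements about retention. The first is a one-sample statement about overall retention: "The randomised sample of 375 patients will provide 80% power to detect a difference of at least 6% or larger" from 75%, that is, 69% or 81%. The second is added to it and concerns the arms. It names the three pathways separately, under 1:1:1 allocation, and says that their comparison "will have >80% power to detect at least 12.2% absolute difference in retention rates between trial arms (or RR=1.16"). The second statement uses the same 75% expectation and a two-sided two-sample test of proportions at the 5% level.

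The predefined statistical analysis plan section compares the randomised groups on 12-month retention by logistic regression, adjusted for the stratification factors. It names no contrast of one arm with two arms combined. Box 2 sets the co-primary retention criterion as "retaining 75% of surviving participants to 12 months postrandomisation", without reference to arm.

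**The concern.** The sentence contains every input needed to check it, and they do not give the power it states. Three separate pathways are named, allocation is equal, and the difference is said to be between trial arms, so the natural reading is 125 against 125. On that reading the power is about ten percentage points below the claim.

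What is at stake is how a reader weighs the between-arm comparison of retention. The trial is not blinded, so differential dropout is worth looking for, and the results are meant to inform a larger trial. From the printed figure a reader would expect a 12.2-point gap between two arms to be missed at most 20% of the time. The design misses it about 30% of the time if one arm lies above 75%, and about 45% of the time if one lies below.

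**Working it through.** **Inputs, all from the section on power for recruitment and retention**

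- 375 randomised 1:1:1, so 375/3 = 125 per arm.
- Reference retention 75%.
- Difference 12.2 points. The ratio fixes the direction: 87.2/75 = 1.163, which agrees with the stated 1.16, whereas 75/62.8 = 1.194 does not.
- Two-sided 5%, two-sample test of proportions, claimed power above 80%.

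**Formula** (normal approximation, pooled variance under the null)

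Power = Φ[(d − 1.96·SE₀)/SE₁], where SE₀ = √{p̄(1 − p̄)(1/n₁ + 1/n₂)}, SE₁ = √{p₁(1 − p₁)/n₁ + p₂(1 − p₂)/n₂}, and p̄ is the weighted mean of p₁ and p₂.

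**Step 1. A comparison that reproduces the stated figure: 250 at 75% against 125 at 87.2%**

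- p̄ = (250 × 0.75 + 125 × 0.872)/375 = 0.7907
- SE₀ = √(0.1655 × 0.012) = 0.04457, and 1.96·SE₀ = 0.0873
- SE₁ = √(0.1875/250 + 0.1116/125) = 0.04053
- Power = Φ[(0.122 − 0.0873)/0.04053] = Φ(0.855) = 80.4%

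The difference detectable with 80% power is 12.15 points (RR 1.162). This matches 12.2, 1.16 and just over 80% together, but it sets one arm against the other two pooled.

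**Step 2. The comparison the text describes: 125 at 75% against 125 at 87.2%**

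- p̄ = 0.811
- SE₀ = √(2 × 0.811 × 0.189/125) = 0.04952, and 1.96·SE₀ = 0.0971
- SE₁ = √{(0.1875 + 0.1116)/125} = 0.04892
- Power = Φ[(0.122 − 0.0971)/0.04892] = Φ(0.510) = 69.5%

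Unpooled variance gives 70.3%, arcsine 70.3%, and exact enumeration of the pooled z test 69.7%.

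**Step 3. The other direction: 125 at 75% against 125 at 62.8%**

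- p̄ = 0.689, SE₀ = 0.05855, 1.96·SE₀ = 0.1148, SE₁ = 0.05804
- Power = Φ[(0.122 − 0.1148)/0.05804] = Φ(0.125) = 55.0%

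**Step 4. What 125 against 125 can detect with 80% power**

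| Direction from 75% | Detectable difference | Other arm |
|---|---|---|
| Upward | 13.6 points (RR 1.18) | 88.6% |
| Downward | 16.6 points | 58.4% |

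Holding 12.2 points upward at 80% power would need 161 per arm, or 3 × 161 = 483 in total.

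**Step 5. Other readings**

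| Reading, 125 per arm | Power |
|---|---|
| Rates symmetric about 75% (68.9% v 81.1%) | 60.6% |
| Two-degree-of-freedom test over three arms, largest gap 12.2 points upward | 58.9% to 76.3% |
| Linear trend 75 / 81.1 / 87.2 | 69.3% |
| Two arms, one-sided 5% | 79.6% (detectable 12.26 points) |

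None of these reaches 80%.

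**The case against.** The best defence is that the figure may be right for a comparison the authors had in mind and did not spell out. The match with 125 against 250 is close and makes this plausible. It remains an inference: the match depends on the pooled-variance formula with the single arm as the higher one, and a one-sided pairwise test comes near too. That test contradicts the stated two-sided one, stays just below 80% and rounds to 12.3, so it does not rescue the sentence. Whatever its source, the number is attached to a comparison between arms that does not have the stated power.

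The second defence concerns consequence, and it stands. A reader might infer that a co-primary outcome is underpowered. The documents do not support that: the co-primary is overall retention, the between-arm statement is an addition tied to no success criterion, and the sample size section says that treatment rates at 12 months helped set the recruitment target. Nor does any section say that a non-significant arm comparison will be read as showing equal retention. Power of 80% would not justify that reading either.

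A reader might also extend the point to the one-sample statement. At 375 the differences detectable with 80% power are about 6.1 points upward and 6.4 downward. Both round to the stated 6%, so that statement is not an error at the precision given. Because retention is defined among survivors, the denominators will be at most 125 per arm. The article gives no expected mortality, so no specific further loss of power can be derived from it.

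**Conclusion.** The statement is wrong as written. For any two arms, power for a 12.2-point difference is about 70% in the direction that the stated ratio implies and about 55% in the other. The honest 80%-power figures are 13.6 points upward and 16.6 downward. This rests only on the article's own inputs: 125 per arm, 75% reference retention, two-sided 5%. All pairwise two-sided methods tried for 75% v 87.2% fall between 69.5% and 70.3%, so the choice of formula does not explain the gap.

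Severity is minor. The upward detectable difference moves by 1.4 points (13.6 − 12.2). The sample size, the co-primary criterion and the planned analysis are unaffected.

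**What to change.** Replace the between-arm sentence with wording to this effect: *a pairwise comparison of arms (125 v 125) has 80% power to detect a 13.6-point increase in retention from 75% (to 88.6%, RR 1.18) or a 16.6-point decrease, two-sided 5%.* Keep 12.2 points only if the authors confirm from their calculation that it refers to one arm against the other two pooled, and then say so in the sentence. A short note that retention is defined among survivors, so that 125 per arm is an upper limit, would be useful.

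The cost is a change of wording and a somewhat less favourable figure. No change to design, sample size or analysis follows.

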#### Power for treatment proportions

Assuming that osteoporosis treatment percentages at 1-year follow-up in the usual care versus active control FRAX-GP versus PHOENIX intervention would be 4.5% vs 15.5% vs 20.3%, respectively (ie, as observed in SCOOP trial vs with expected improvement in PHOENIX), a total of 375 participants recruited and randomised in the ratio 1:1:1 will have 96% power (figure 4G) to detect linear trend in treatment proportions based on a two-sided test of binomial proportions at 5% statistical significance level. The same sample size will have 93% power for a secondary two-degree of freedom test of between-group contrasts in comparison with usual care. When allowing for up to 25% attrition due to non-differential dropout or incompleteness of outcomes, the remaining sample size of 280 participants will have >84% power to detect the same magnitude of differences (figure 4G).

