**Trial registration number:**

ISRCTN14722819.

Strengths and limitations of this studyFirst osteoporosis screening study involving patients attending radiology CT waiting areas.Individuals randomised to either comprehensive screening for osteoporosis (by applying Fracture Risk Assessment questionnaire, CT bone densitometry and CT vertebral fracture detection) or usual care.Allows patients the flexibility to self-consent, and tests both the willingness of CT attenders to consent, CT technologies and information flow between trial centres and Cambridge hub.Limited by an amendment of the primary outcome measure because recruitment during COVID-19 pandemic predicted skew towards the more seriously ill (via cancellation of non-urgent and routine scans).Modifications to both the retention outcome and longer recruitment window were made to take account of pandemic redeployment of medical research team.Missing a secondary care direct intervention arm, which would relieve some of the burden from primary care to enact osteoporosis treatments.

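### Retention is judged on 75% of survivors but the sample size counts losses against all 375 randomised, so meeting the co-primary does not secure the 280 evaluable patients behind the >84% power

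*Protocol article*

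**What the plan says.** Box 2 of the Protocol article gives the retention co-primary as "defined as retaining 75% of surviving participants to 12 months postrandomisation", shown by an answer to the yes/no question on bone active medication in the 12-month questionnaire. The abstract and the opening of Methods and analysis use the same survivor denominator. The strengths-and-limitations list says that a primary outcome measure was amended because "recruitment during COVID-19 pandemic predicted skew towards the more seriously ill", and that the retention outcome was modified. Survival at 12 months is a listed secondary outcome, but no expected mortality is given.

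The sample-size text uses a different base. Under Power for recruitment and retention, "The randomised sample of 375 patients will provide 80% power" to detect a 6-point departure from 75% overall retention, that is, to 69% or 81%. Under Power for treatment proportions, the assumed rates "would be 4.5% vs 15.5% vs 20.3%, respectively" (usual care, FRAX to GP, PHOENIX) lead to the statement that "a total of 375 participants recruited and randomised in the ratio 1:1:1 will have 96% power" for a linear trend, and "93% power for a secondary two-degree of freedom test of between-group contrasts in comparison with usual care". The attrition statement follows: "When allowing for up to 25% attrition due to non-differential dropout or incompleteness of outcomes, the remaining sample size of 280 participants", with power above 84%.

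**The concern.** The same 75% is applied to two denominators. The 280 is about 75% of the 375 randomised, so it leaves room for 95 losses of every kind. The co-primary allows 25% non-response among survivors in addition to any deaths. Because the retention item and the treatment outcome are the same questionnaire answer, a retained participant is an evaluable one, and the two statements can be compared directly.

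The study could therefore report its retention co-primary as met while holding fewer evaluable patients than its own power statement assumes. The article says that treatment rates were used to help set the recruitment target and will inform power for any later trial, so an attrition model with no explicit place for deaths could be carried forward. The population is women aged 65–90 and men aged 75–90 having CT for any clinical reason, so deaths within 12 months cannot be assumed negligible.

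**Working it through.** **Inputs from the article.** N = 375, allocated 1:1:1; treatment rates 4.5%, 15.5% and 20.3%; two-sided 5%; 25% attrition; retention threshold 75% of survivors; retention null 75%, alternatives 69% and 81%.

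**Assumed input.** 12-month mortality m of 5, 10 and 20%, because the article gives none.

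**1. Reproducing the stated figures**

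- Evaluable: 375 × 0.75 = 281.25 (stated 280).
- Two-degree-of-freedom Pearson test, non-central chi-square. The mean rate is (0.045 + 0.155 + 0.203)/3 = 0.1343. The squared deviations sum to 0.01312, and 0.1343 × 0.8657 = 0.1163. The non-centrality is n per arm × 0.01312/0.1163. At 125 per arm it is 14.1, giving 93.0% (stated 93%). At 280/3 per arm it is 10.5, giving 83.6% (stated above 84%).
- Linear trend (Cochran–Armitage, scores 0, 1, 2), power = Φ[(T − 1.96√V0)/√V1], with T = n × (0.203 − 0.045), V0 = 2n × 0.1163 and V1 = n × (0.045 × 0.955 + 0.203 × 0.797) = 0.2048n. At n = 125 this is (19.75 − 10.57)/5.06 = 1.81, giving 96.5% (stated 96%). At N = 280 it is 90.0%.

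The figure of just over 84% is thus close to the two-degree-of-freedom result. The trend test clears it with room to spare.

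**2. When the co-primary stops securing 280**

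- One death: 374 × 0.75 = 280.5, so 281 answers are needed.
- Two deaths: 373 × 0.75 = 279.75, so 280 are needed.
- Three deaths: 372 × 0.75 = 279, so the criterion is met with 279.

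**3. Power when retention is exactly at the threshold**

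Evaluable = 375 × (1 − m) × 0.75. The last column is the survivor retention needed for 280, that is 280/[375 × (1 − m)].

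| Assumed mortality | Survivors | Evaluable | 2-df power | Trend power | Survivor retention needed for 280 |
|---|---|---|---|---|---|
| 5% | 356 | 267 | 81.7% | 88.6% | 78.6% |
| 10% | 337 | 253 | 79.5% | 86.8% | 83.0% |
| 20% | 300 | 225 | 74.3% | 82.5% | 93.3% |

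Trend power is 84.8% at 15% mortality and reaches 84.0% at 234 evaluable, where mortality is 1 − 234/281.25 = 16.8%.

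Simulation gives higher power. The two-degree-of-freedom test has about 89% at 280 and about 87, 85 and 80% at the three sizes. The trend test has about 91% at 280 and about 90, 88 and 84%.

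**4. One-sample retention test**

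Power = Φ[(0.06√n − 1.96√(0.75 × 0.25))/√(p1(1 − p1))].

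- n = 375, p1 = 0.69: (1.162 − 0.849)/0.462 = 0.677, giving 75.1%.
- n = 375, p1 = 0.81: 0.313/0.392 = 0.798, giving 78.8%.
- With survivors as n (356, 337, 300), power for the fall to 69% is 73.0, 70.8 and 66.0%.

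Of the gap between 80% and these values, about 5 points exist with no deaths at all (80 − 75.1). Deaths add 75.1 − 73.0 = 2, 75.1 − 70.8 = 4 and 75.1 − 66.0 = 9 points.

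**The case against.** The attrition sentence is conditional: if up to a quarter are lost, 280 remain. Nothing in the article says that meeting the co-primary guarantees 280, and a death before the questionnaire can fairly be read as an incomplete outcome. This stands as a defence of that sentence taken alone. It does not reconcile the two statements: if the 25% includes deaths, the co-primary still allows 25% non-response on top of them.

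The losses of power are also smaller than they may look. The article puts the trend test first and calls the other test secondary. In simulation the trend test still has about 84% power at 225 evaluable, and the two-degree-of-freedom test stays above 84% to about 10% mortality. That is a fair point about actual performance. However, simulated two-degree-of-freedom power at 375 is about 97%, not the stated 93%, so the plan's own figure is on the non-central chi-square scale and should be restated on that scale. In the other direction, a trend calculation using the null variance alone gives 88.6% at 280 and drops below 84% at about 13% mortality. The point does not rest on that more pessimistic form.

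Finally, non-responders are to be telephoned, so survivor retention may exceed 75%. That may close the gap in practice, but at 10% mortality 83.0% of survivors would be needed.

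**Conclusion.** The mismatch is real and its consequence is modest. The co-primary is defined on survivors, both power statements are computed on all 375, and 280 evaluable is not secured once three participants have died. The size depends on a mortality the article does not give and on retention exactly at the threshold. Over an assumed 5–20%, evaluable numbers run from 267 to 225, two-degree-of-freedom power from 81.7 to 74.3%, and trend power from 88.6 to 82.5%. For the trend test, the claim of more than 84% fails only above roughly 15–17% mortality.

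Four stronger readings are tempting and are not supported:

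- That any death at all takes the number below 280. The rounding from 281.25 absorbs the first two.
- That deaths explain why the retention test misses 80%. Most of the shortfall at 5 or 10% mortality is already present at n = 375.
- That the feasibility decision is compromised. The co-primaries are thresholds, treatment rate is a secondary outcome, and neither threshold depends on the 84%.
- That the pandemic amendment introduced the survivor denominator and the power text was left behind. The article does not give the previous wording of the retention outcome.

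**What to change.** - In Power for treatment proportions, define attrition as death plus non-response. Give evaluable N as 375 × survival × retention and state power over a named mortality range, for example 5–20%, separately for the trend and two-degree-of-freedom tests.
- In Power for recruitment and retention, use expected survivors as the denominator. Correct the baseline at n = 375, which is about 75% for a fall to 69% and 79% for a rise to 81%.
- Beside the co-primary, note that retaining 75% of survivors does not secure 280 evaluable participants.

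The cost is a few rewritten sentences and slightly less favourable stated figures. No additional participants are required.
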